#### Secondary Outcomes

Chi-squared (χ2) tests will be used to assess the relationship between re-attempts and qualitative variables; independent *t*-test and Mann-Whitney will be used to compare parametric and non-parametric variables between the two groups of re-attempts and no re-attempts. Variables with a *P*-value lower than 0.2 will be included in a multiple Cox regression model to estimate the adjusted hazard ratio (AOR) with a 95% confidence interval (CI) for the risk factors associated with re-attempt suicide. In all the tests, the confidence interval will be 95%, and *P* < 0.05 to be considered significant.

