#### Psychometric Measures and Clinical Factors

Personal and family medical history, current psychiatric diagnosis and treatments, method of attempted suicide will be collected. Psychometric assessments will be performed using a detailed assessment form containing a battery of validated self-administered questionnaires in their French translation. The following dimensions will be documented: depressive symptoms severity with the Quick Inventory of Depressive Symptomatology (QIDS-SR16) (25), risk for bipolar disorder with the Mood Disorder Questionnaire (MDQ) (26), risk for psychosis with the Prodromal Questionnaire-Brief (PQ-B) (27), hazardous alcohol consumption with the Alcohol Use Disorders Test (AUDIT) (28), nicotine dependence with the Fagerstrom Questionnaire (29), cannabis abuse with the Cannabis Abuse Screening Test (CAST) (30) and the Cannabis Use Disorders Identification Test, revised (CUDIT-R) (31), impulsiveness with Barratt Impulsiveness Scale (BIS-10) (32), anger with the State-Trait Anger Expression Inventory 2 (STAXI-2) (33), childhood traumatic experiences with the Childhood Trauma Questionnaire (CTQ) (34), protective factors against suicidal behaviors with the Reasons For Living (RFL) inventory (35).

Moreover, patients will complete non-validated self-reports: visual analog scales for subjective moral pain, physical pain, suicidal ideation intensity, and a 12-item questionnaire on negative life events during the last 6 months.

The Columbia Suicide Severity Rating Scale (C-SSRS) will be administered by a trained clinician. The C-SSRS is a semi-structured interview with solid psychometric properties designed to assess grading of suicidal ideation and behaviors, validated in various general and clinical populations, including adolescents and adults presenting for psychiatric care (36). In a recent study by Lindh et al. (37), C-SSRS appears to perform well in predicting suicide attempts within 3 months, compared to other suicide risk scales.

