### Statistical Analysis

Statistical analysis will be performed using R software version 4.02. The significance level alpha will be set at 0.05, and all statistical tests will be 2-tailed.

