#### Sample Size Calculation

Based on the largest survey study conducted in France by Vuagnat and colleagues (2019) (4), we estimated that 12.4% of the population will be readmitted for suicidal attempt within the 3 months following a first suicide attempt that led to hospitalization. This is also in accordance with the study from Spirito and colleagues (2003) (6) conducted in a comparable sample of youth individuals (12%). Using the Wald Confidence Interval method, we calculated that a sample of 200 participants will be sufficient to reach a precision of +/– 4% calculated as 95 CI = p +/– 1.96 sqrt (p (1–p)/n), with *p* = 0.124.

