BDNF is able to cross the blood-brain barrier and its plasma levels reflect the central nervous system levels (52). In addition, studies suggest that the mature form of BDNF and its precursor pro-BDNF could have opposite functions on neural plasticity: while mature BDNF promotes neuronal survival and growth, pro-BDNF induces neuron apoptosis (53). It thus appears essential to measure not only total BDNF, which does not reflect this balance between pro-BDNF and mature BDNF.

For the past few years, the immune system has been a growing focus of interest in suicide biomarker research. Particularly, studies have suggested a dysregulation of anti- and pro-inflammatory cytokine balance (54, 55). However, in a recent systematic review (56), the role in suicidal behaviors of central and peripheral interleukins, their genes and polymorphisms, remained inconclusive. The authors underline the heterogeneity of the samples, as well as potential confounding factors of inflammation, which are often not taken into account. As an exploratory measure of peripheral inflammation, we have chosen to measure the levels of IL-6, one of the most studied pro-inflammatory cytokines. Additionally, we will measure fibrinogen, orosomucoid, and CRP, three non-cytokinic inflammatory factors. CRP is an acute-phase inflammatory protein synthesized in response to serum IL-6 increase (57) which has been associated with suicide (15, 16), whereas fibrinogen and orosomucoid are two other acute-phase proteins which has not yet been investigated in suicidal behaviors. For further studies, others peripheral non-cytokinic biomarkers of interest are serum S100B, that have been associated with suicidal ideation and behaviors in adolescents (58), and the renin-angiotensin system, at the interface between inflammation and the HPA axis, with polymorphisms of the angiotensin-I converting enzyme associated with suicide attempts and completions (59). Interestingly, combining different inflammatory markers into an inflammatory index as did O'Donovan et al. (16) could be a valuable approach.

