## Trial Status

The recruitment of patients into the trial began in May 2018 and is scheduled to end in October 2022. Preliminary analyses conducted on a sample of the 73 first patients of the cohort (70.8% females; mean age: 19.72 years, SD 2.44) revealed a re-attempt rate at 3 months of 17.81%, supporting a trend toward a higher risk of suicide re-attempt in this population as compared with the literature on adults.

V7 (12/07/2021): MS5 Addition of several blood tests; update of associated investigators and other study stakeholders, update of scientific collaborators.

V6 (04/22/2021): MS4 18 months extension of the recruitment period of the study, as a consequence of COVID-19.

V5 (03/30/2020): MS3 12 months extension of the recruitment period of the study.

V4 (06/03/2019): MS2 12 months extension of the recruitment period of the study.

V3 (07/26/2018): MS1 modification of the inclusion criteria, extension of the study to minors from 16 years of age, and 6 months extension of the recruitment period of the study.

V2 (02/08/2018): Approval of the initial protocol by the ethics committee.

V1 Initial protocol before submission to the ethics committee.

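### Screening about 40 baseline variables at P < 0.2 into one Cox model with about 25 events, then reading P < 0.05 as significant, leaves false predictors uncontrolled

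*Protocol article*

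**What the plan says.** Under Secondary Outcomes, the Protocol article compares re-attempters with non-re-attempters one variable at a time, by chi-squared, t or Mann-Whitney test. Variables with a P-value "lower than 0.2 will be included in a multiple Cox regression model to estimate the adjusted hazard ratio (AOR"). No other route into the model is given. On how results are read, the same paragraph says "In all the tests, the confidence interval will be 95%, and" takes P < 0.05 as significant. The general Statistical Analysis paragraph adds: "The significance level alpha will be set at 0.05, and all statistical tests will be 2-tailed".

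The candidate pool is wide. The Outcomes section makes the baseline socio-demographic, clinical and biological factors the secondary outcomes without narrowing them. On the clinical side alone, "Psychometric assessments will be performed using a detailed assessment form containing a battery of validated self-administered questionnaires", and further ratings and about ten laboratory measures are added.

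The study size was set for the incidence estimate, not for this model: "a sample of 200 participants will be sufficient to reach a precision of +/– 4" per cent. The assumed rate is given as "we estimated that 12.4% of the population will be readmitted for suicidal attempt within the 3 months". Trial Status reports that the first 73 patients "revealed a re-attempt rate at 3 months of 17.81" per cent.

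**The concern.** The same outcome data both choose the variables and test them, and the test is read at its nominal level. A noise variable that enters the model has already shown P < 0.2, so its chance of also showing P < 0.05 is far above 5%. With some 40 candidates and about 25 events, several noise variables can be expected in the model. Estimates chosen this way tend to be too large, and their ordinary 95% intervals cover less often than stated.

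The screen can also fail in the other direction. The Discussion names depression as a possible confounder of the cortisol measures and says the analysis will take it into account. Under the stated rule, depression would be left out of the model whenever its own univariate P-value is 0.2 or more.

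At stake is which factors the study reports as linked to early re-attempt. The Abstract hopes that these will find clinical use.

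**Working it through.** **Study size.** The article's own precision formula gives 1.96 × √(0.124 × 0.876 / 200) = 4.57%, not 4%. That mismatch is a separate matter and nothing below depends on it.

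**Events.** 200 × 0.124 = 24.8. At the interim rate (13/73 = 17.81%), 200 × 0.1781 = 35.6. The Discussion says drop-out was not allowed for, so losses would lower either figure.

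**Candidates**, counting each scale once. The article gives no total, so this count is ours:

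- Socio-Demographic Factors: 11, or 12 if the two named psychosocial issues are separated.
- Clinical history: 5 (personal history, family history, diagnosis, treatments, method).
- Scales and ratings: 11 self-report questionnaires, the C-SSRS, 3 visual analog scales and 1 life-events questionnaire = 16.
- Biological Factors: 8 to 10 (CRP, orosomucoid, fibrinogen, blood cortisol, IL-6; toxoplasma IgG and IgM as 1 or 2; BDNF isoforms as 1 or 2; hair cortisol).

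Low: 11 + 5 + 16 + 8 = 40. High: 12 + 5 + 16 + 10 = 43. Subscales, dummy variables and the 12 separate life-event items would add more.

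**Events per variable.** Per candidate: 24.8 / 40 = 0.62. If nothing has an effect, the screen passes 0.2 × 40 = 8 variables (8.6 of 43). Per retained variable: 24.8 / 8 = 3.1, or 35.6 / 8 = 4.5 at the interim rate (2.9 and 4.1 with 8.6 variables).

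**Rough error rate.** For 40 independent null tests, 1 − 0.95^40 = 87.1%. For a single noise variable that has passed the screen, the chance of P < 0.05 is roughly 0.05 / 0.20 = 25%.

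**Simulation of the stated rule.** Each of 1,000 runs had n = 200, exponential times censored at 3 months, and no true effects. About 35% of candidates were binary. Screening was by chi-squared or t-test at P < 0.2, all survivors entered one Cox model, and Wald tests were read at P < 0.05. The correlations and the binary share are assumptions, because the article gives neither.

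| Candidates | Event rate | Common correlation | At least one false predictor | Mean number false |
|---|---|---|---|---|
| 40 | 12.4% | 0 | 83.7% | 2.13 |
| 43 | 12.4% | 0 | 85.1% | 2.17 |
| 43 | 17.8% | 0 | 84.5% | 2.28 |
| 30 | 12.4% | 0 | 72.5% | 1.49 |
| 20 | 12.4% | 0 | 58.8% | 0.97 |
| 55 | 12.4% | 0 | 89.7% | 2.88 |
| 40 | 12.4% | 0.3 | 64.3% | 1.25 |
| 40 | 12.4% | 0.5 | 47.6% | 0.80 |

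A separate set of 300 runs, also with 35% binary candidates, gave 84% (mean 2.1) for independent candidates, 68% at correlation 0.3 and 41% at 0.5.

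In the first row, 8.1 variables were retained on average (5th to 95th percentile 4 to 13), and 2.13 / 8.1 = 26% of them were read as significant, in line with the 25% above. The chance of at least one univariate P < 0.05 in the same runs was 87.9%, so the Cox step gives little protection. More events do not help either: the 17.8% row is almost the same as the 12.4% row, because the problem is multiplicity and selection as well as sparse data.

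**The case against.** The strongest reply is that this part of the study is exploratory, and the article says so: the Abstract words the secondary objective as exploring risk factors, and the BDNF, IL-6 and other biological measures are described in similar terms. The primary objective is incidence, which the rule does not touch. The mention of clinical use is a hope, not a claim. This stands, and it lowers the severity. It does not remove the point, because Secondary Outcomes still applies P < 0.05 without qualification.

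Several stronger readings are tempting but are not supported:

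- A reader might infer that most predictors the study reports will be false. Every figure here assumes that no candidate has any effect. The Introduction lists previously identified risk factors, many of them measured in this study, and no mixture of true and null predictors was simulated. The false share among reported predictors is therefore unknown.
- A reader might quote a false-positive chance near 90%. That needs unfavourable assumptions, such as 55 independent candidates. Correlation lowers the figure, and at 0.5 it is about an even chance or less. A correlation that high across items as unlike as urbanicity, toxoplasma serology and alcohol use is unlikely, but it cannot be excluded from the article.
- A reader might fault the article for giving no cap on model size, no collinearity handling and no validation. A condensed article commonly leaves these to the full protocol or analysis plan. The criticism here is of the selection rule that is stated.
- Screening with tests that ignore follow-up time, before a Cox model, looks inconsistent. With a fixed 3-month window the difference should be small.

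The Discussion also says that depression and psychiatric diagnoses will enter the analysis, which suggests that selection is not meant to be purely data-driven. Secondary Outcomes provides no means for this, so the two sections need to be reconciled.

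**Conclusion.** The point holds and should be fixed. As written, the rule sends any of 40 to 43 candidates with P < 0.2 into one Cox model supported by about 25 events (about 36 at the interim rate) and reads the result at an uncorrected 0.05. About 8 noise variables would pass, at 3 to 4 events each. Under a global null, the chance of at least one falsely significant predictor is about 84% for independent candidates, 64–68% at common correlation 0.3 and 41–48% at 0.5, against a nominal 5% per test. Post-selection hazard ratios and their 95% intervals are biased as well; the size of that bias was not established here.

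These figures rest on the global null, on assumed correlations, on the assumed mix of binary and continuous variables, and on our count of candidates. The conclusion does not depend on the exact count: with only 20 independent candidates the chance is still 59%.

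**What to change.** In Secondary Outcomes, delete the P < 0.2 screen. Before the final analysis:

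1. Combine redundant measures: keep one of the two cannabis scales, and form one index from CRP, fibrinogen, orosomucoid and IL-6. The Discussion already sees merit in "combining different inflammatory markers into an inflammatory index".
2. Pre-specify, on subject-matter grounds, a small predictor set sized to the expected number of events, with depression included wherever cortisol is assessed. Fit it with a penalised Cox model (Firth or ridge).
3. Report all remaining candidates only as univariable Cox estimates with false-discovery-rate control, labelled exploratory, and do not call P < 0.05 significant there.

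This needs no new data, only a change of analysis wording and standard software. The price is fewer nominally significant predictors.

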## Discussion

The main purpose of the SURAYA study is to assess the incidence of suicide re-attempt after a first attempt in a cohort of young people aged 16 to 25. The study's main strength is the homogeneity of participants: a narrow age group relevant to a critical period of neurodevelopment, and an incipient cohort in terms of onset of suicidal behaviors. There is little research focusing on suicidal behaviors in adolescents and young adults, and we do not currently know whether this group is at a higher risk of early suicide re-attempt compared to a general adult population.

Taken separately, most suicide risk factors previously identified are reported to be weak predictors of later suicidal ideation and behavior. In order to gain a comprehensive view of the potential prognostic factors of suicide re-attempts, we carefully collected a wide range of socio-demographic, clinical, and biological data relevant to suicidality; we used both self- and clinician-administered validated scales for more reliability across psychometric evaluations. We emphasized on emerging psychiatric disorders, addictions, psychotrauma, impulsivity and anger, environmental triggering factors, and severity of the first suicide attempt with the C-SSRS.

Beyond these features, we chose to include participants regardless of their psychiatric diagnosis, to capture transnosographic correlates of suicide re-attempts, and thus minimize the effect of potential confounding factors of comorbid psychiatric disorders. However, ICD10 diagnostic criteria will be included in the analysis of conditions such as depression or borderline personality disorder being particularly prevalent in the included population. Attenuated psychotic symptoms (i.e., ultra-high risk population), measured by the PQ-B, are also an interesting symptomatic dimension, as the onset of the disorder can frequently be manifested by an act of aggression. A recent meta-analysis of suicide risk during this time period suggests that suicidal and self-harming thoughts and behaviors were highly prevalent in the ultra-high risk population (40).

Impulsivity can be described as a general pattern of behavior (trait-impulsivity), as responses that are not conformed to their context (action-impulsivity), or as inability to delay reward or to take future consequences into account (choice-impulsivity). Due to a delayed development of top-down prefrontal areas relative to subcortical regions involved in desire and fear, adolescents and young adults are particularly susceptible to impulsive behaviors (41), which suggests an increased risk of suicidal behaviors. This dimension therefore constitutes an interesting criterion for suicide re-attempt (42).

For biological measures, we will explore whether suicide re-attempt could be associated with alterations of the HPA axis, neuroplasticity, and inflammation, including a recent toxoplasmosis infection. These biological systems are highly connected since glucocorticoids dysregulation could lead to increased inflammatory activity and impaired neuroplasticity (43, 44).

Cortisol is the key hormone of the stress-response system, and failure of the HPA axis in response to stress may underlie suicidal crises (22). Most findings, conducted in the general population, suggest that both lower and higher baseline and stressor-induced cortisol levels have been associated with suicide, consistent with allostatic load theories resulting from the adaptation to the environment (22, 45). Accordingly, we will quantify blood cortisol levels as a measure of an acute stress provoked by the suicide attempt, and, in collaboration with the University Hospital of Bordeaux, we will assess hair cortisol, as a retrospective indicator of cumulative cortisol levels during the last 3 months preceding the attempt. To date, hair cortisol has been used in various settings as a reliable marker of long-term exposure to stress (46–48). A recent meta-analysis investigating the association between hair cortisol levels and depression found contradictory results (49). Nonetheless, because altered functioning of the HPA axis has been strongly involved in major depressive disorder (50), depression is a potential confounding variable of cortisol measures and will be considered in the analysis. Similarly, thyroid dysfunction may result in depressive symptoms (51). Thyroid function tests were not systematically performed in the cohort, thus we cannot rule out depression with subclinical hypothyroidism.

BDNF is able to cross the blood-brain barrier and its plasma levels reflect the central nervous system levels (52). In addition, studies suggest that the mature form of BDNF and its precursor pro-BDNF could have opposite functions on neural plasticity: while mature BDNF promotes neuronal survival and growth, pro-BDNF induces neuron apoptosis (53). It thus appears essential to measure not only total BDNF, which does not reflect this balance between pro-BDNF and mature BDNF.

For the past few years, the immune system has been a growing focus of interest in suicide biomarker research. Particularly, studies have suggested a dysregulation of anti- and pro-inflammatory cytokine balance (54, 55). However, in a recent systematic review (56), the role in suicidal behaviors of central and peripheral interleukins, their genes and polymorphisms, remained inconclusive. The authors underline the heterogeneity of the samples, as well as potential confounding factors of inflammation, which are often not taken into account. As an exploratory measure of peripheral inflammation, we have chosen to measure the levels of IL-6, one of the most studied pro-inflammatory cytokines. Additionally, we will measure fibrinogen, orosomucoid, and CRP, three non-cytokinic inflammatory factors. CRP is an acute-phase inflammatory protein synthesized in response to serum IL-6 increase (57) which has been associated with suicide (15, 16), whereas fibrinogen and orosomucoid are two other acute-phase proteins which has not yet been investigated in suicidal behaviors. For further studies, others peripheral non-cytokinic biomarkers of interest are serum S100B, that have been associated with suicidal ideation and behaviors in adolescents (58), and the renin-angiotensin system, at the interface between inflammation and the HPA axis, with polymorphisms of the angiotensin-I converting enzyme associated with suicide attempts and completions (59). Interestingly, combining different inflammatory markers into an inflammatory index as did O'Donovan et al. (16) could be a valuable approach.

The neuroimmune network hypothesis proposes reciprocal interactions between the immune system and the brain. In addition to activation of the HPA axis, peripheral cytokines are able to reach the brain through humoral, neural, and cellular pathways (60). Functional neuroimaging studies in adults suggest that systemic inflammation is associated with altered resting state functional connectivity (RSFC) within several brain networks associated with cognition and mood regulation (61–63). Notably, Marsland and colleagues (2017) (61) showed that within the default mode network (DMN), higher levels of IL-6 were positively correlated with connectivity of the subgenual anterior cingulate cortex and negatively correlated with the dorsal medial prefrontal cortex. Another study reported that induced inflammatory state was associated with decreased connectivity between salience network regions, including the insula, amygdala, dorsal anterior cingulate cortex, and anterior prefrontal cortex (63). Few studies have examined these associations in youth, yet scarce data point to different networks than adult studies (64, 65). Likewise, little is known about the functional connectivity patterns associated with suicidal behaviors in adolescence and young adulthood, which contrasts with the substantial changes of these RSFC during this unique neurodevelopmental phase (66). Interestingly, recent studies comparing young depressed patients with or without a history of suicide attempt showed reduced connectivity between the anterior DMN and the salience network (67), and decreased RSFC between left prefrontal-right anterior cingulate cortices, the latter being related to higher trait-impulsivity in attempters (68). Long-term alterations of functional connectivity could lead to structural changes in underlying brain areas (69). Of particular interest to our study, one prospective study showed that reduced baseline gray matter volume and white matter integrity in frontal areas differentiated adolescents and young adults with mood disorders who later attempt suicide (70), highlighting the need to combine neuroimaging markers with other biopsychosocial markers in future studies.

When interpreting our results, we will take into account potential limiting factors. First, since all inclusions will take place in Edouard Herriot University Hospital, we expect a center-effect bias. Inpatients of our unit may have more severe disorders and suicidal behaviors. Besides, patients admitted to the unit do not exhibit severe behavioral problems nor are hospitalized without consent, which may exclude a certain group of suicide attempters. This could lead to a lack of representativity and limit the external generalizability of the results. Second, loss to follow-up is common in longitudinal studies and could potentially cause selection bias. In our study, we have not included the risk of drop-outs in the calculation of the number of subjects needed. However, a follow-up period extending over a relatively short period of 3 months could reduce loss to follow-ups. To further limit this bias, we prefer phone calls at 3 months over face-to-face consultations. If the patient could not be reached, we set up a 3-level data retrieval process by gathering information from his/her designated trusted person, contacting his/her primary care physician, and finally by consulting his/her medical records. In further cases of inability to obtain information, we have planned a statistical management of missing data. Third, COVID-19 pandemic occurred during the inclusion phase. Recruitment was slowed down due to fluctuating demand for access to care, and to the reorganization of the Department of Psychiatry in our University Hospital. Psychosocial distress due to the pandemic and its consequences could modify suicidal behaviors (71). In addition, there may be stress and inflammation confounding bias related to the COVID-19 status of some inpatients. From March 2020, every patient underwent a SARS-CoV-2 RT-PCR upon admission and only those who were negative were hospitalized in the unit, thus, there was no COVID-19 positive inclusion in this study. Nonetheless, we cannot rule out the possibility of such patients being included prior to the systematic implementation of COVID-19 testing, when the virus circulation was lower in France, i.e., from approximately November 2019 to February 2020. *Post-hoc* subgroup analyses could be needed to assess the impact of potential COVID-19 infection during this time period. Either way, it would be interesting to compare the repercussions of the COVID-19 pandemic on the onset of suicidal behaviors in a future study.

Since preventive interventions have successfully managed to reduce suicide mortality in the general population (72), we hope that the findings of this study will pave the way for early and targeted interventions in youth.

